**Table 2 Tab2:**
[figure not shown]
Trial schedule University Medical Center Mainz and University Rostock

^a^Schedule for each subject

^b^The Florbetaben-PET can be postponed to the post-cognitive-training phase or the follow-up phase

Abbreviations: *MRI*  magnetic resonance imaging, *fMR*I functional magnetic resonance imaging, *PET* positron-emission tomography, *ApoE4*  apolipoprotein E4, *CETP* Cholesteryl Ester Transfer Protein, *SNP*  single nucleotide polymorphism, BDNF brain-derived neurotrophic factor

To investigate the impact of a physical training (combined aerobic and coordination training, ACT) on transfer of cognitive training gains in HOA (secondary outcome), subjects recruited at the center in Cologne will undergo an extended experimental protocol with two additional phases prior to the pre-cognitive-training phase (pre-ACT-training phase, ACT-training phase). The primary protocol (as shown in Table 3) will be complemented by a 20-week physical training period and an evaluation of the physical fitness, as well as an additional MRI scan evaluation (see Table 3).

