### Population

#### Sample size

It is planned to include 237 cognitively healthy elderly subjects (aged 60 years and older) in total distributed over the three trial sites, satisfying the statistical power requirements for different research questions, as described below. Paticipants will be recruited by local newspaper announcements and flyers.

For the investigation of the primary objective, a sample size of 160 subjects has been determined based on a power calculation (see “Statistics”). Assuming a dropout rate of about 15%, the recruitment of subjects will be distributed as follows: Mainz: *N* = 60, Rostock: *N* = 60, German Sport University Cologne/University Hospital Cologne: *N* = 72.

For the investigation of the predictive value of a preceding ACT for the transfer of cognitive training gains in HOA (secondary objective), all 72 subjects recruited at the German Sport University Cologne/University Hospital Cologne (who are also part of the investigation of the primary outcome) will undergo an extended experimental protocol, including ACT followed by the cognitive training. The sample size of 72 subjects has been determined based on a power calculation (see “Statistics”). Since, so far, no evidence has been published showing that physical activity may have an impact on transfer via mechanisms other than brain structure and function, it is assumed that the preceding physical training in subjects recruited in Cologne will not confound the investigation of the primary objective.

To minimize/avoid bias, the following control subjects will be included: 15 HOA will be enrolled in Cologne undergoing the standard experimental protocol without ACT to assure that the net effect of the cognitive training does not differ from the effects at the other trial sites. To control performance alterations in the neuropsychological examinations for retest effects, an additional sample of 30 HOA, generated in Mainz (*N* = 10), Rostock (*N* = 10), and German Sport University Cologne/University Hospital Cologne (*N* = 10), will undergo the repeated neuropsychological examinations without cognitive training.

Within each trial site, participants will be distributed randomly to experimental or control groups, stratified centrally by the trial coordinator at the trial site University Medical Center Mainz. The study code is centrally managed by this trial site. Participants will be enrolled by their respective trial site.

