#### Genetics

Two samples of 5 ml ethylenediamine tetraacetic acid blood will be collected from participants at the pre-training phase and at the post-training phase in Mainz and Rostock and at the pre-ACT-training phase, post-ACT-training phase, and post-cognitive-training phase in Cologne. Blood samples will be kept on ice for a maximum of 15 min and subsequently stored at − 80 °C in the recruiting centers. Frozen blood samples will be shipped on dry ice to the Laboratory of Molecular Genetics, Institute of Human Genetics, University Medical Center Mainz. There, deoxyribonucleic acid (DNA) extraction from one of the frozen blood samples taken at the pre-training phase will be performed on a chemagic Magnetic Separation Module I using the chemagic DNA Blood Kit special for the automated isolation of DNA from 5 ml whole blood followed by quantification of DNA on a NanoDrop 2000UV-Vis spectrophotometer. Genotyping for the single nucleotide polymorphisms rs7412 and rs429358 in the apolipoprotein E gene, rs5882 and rs1800775 in the *Cholesteryl Ester Transfer Protein* gene, rs6265 in the *BDNF* gene, rs2765 in the *Neurokinin.3 Receptor* gene, rs6439886 in the *Calsyntenin 2* gene, and rs17070145 in the *Kidney and Brain Expressed Protein* gene will be carried out from extracted genomic DNA samples using polymerase chain reaction followed by pyrosequencing on a Pyromark Q96 ID Instrument using PyroMark Gold Q96 SQA Reagents and the Pyromark Q96 ID software. The second blood sample taken at the pre-training phase and both blood samples taken at the post-training phase will be stored at − 80 °C for prospective analyses of training-induced epigenetic and transcriptome changes. Blood samples will be stored in secured rooms at the Institute of Human Genetics of the University Medical Center Mainz for a maximum of 60 years.

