### Statistics

#### Sample size

Primary outcome: the analyses will focus on training gain transfer (defined as a binary criterion for each subject) and simultaneously incorporate measures of corpus callosum integrity and bihemispheric processing. The sample size calculation was performed based on main effects analyses where the effects of both measures will be considered as main effects. Assuming a transfer rate of cognitive training gains of about 15% for participants with low corpus callosum integrity, and a transfer odds ratio of 3 for participants with high corpus callosum integrity, a sample size of 160 provides a power of 0.8 at a significance level of 0.05 for a Wald Test in a logistic regression model. Assuming a dropout rate of about 15%, a total of 192 participants need to be included.

Secondary outcome: for evaluating physical training as a potential modulator of cognitive training gain transfer, ACT-induced fitness changes will be analyzed with respect to changes of corpus callosum integrity, as well as with respect to effects on transfer. The former analysis corresponds to considering the correlation between fitness changes and integrity changes. For the latter, an interaction between corpus callosum integrity and fitness changes with respect to transfer will be considered in a logistic regression model. Such an interaction can be expressed as a correlation between fitness changes and the degree of transfer in a group with low/high corpus callosum integrity. Based on the results by Voss et al. [14], we assume a correlation of about 0.43 between both measures. At a significance level of 0.05, 30 individuals per (equally sized) integrity group are needed to detect such a correlation with a power of 0.8. As a result, ACT needs to be performed for 60 individuals in total. Assuming a dropout rate of about 15%, 72 subjects at the German Sport University Cologne will undergo the extended experimental protocol.

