#### Analysis of secondary endpoints

For evaluating physical training as potential modulator of cognitive training gain transfer, correlations between fitness changes and integrity changes of the corpus callosum will be applied. Moreover, an interaction between corpus callosum integrity and fitness changes with respect to transfer will be considered in a logistic regression model. Such an interaction can be expressed as a correlation between fitness changes and the degree of transfer in a group with low/high corpus callosum integrity.

To evaluate the predictive value of brain vascular lesion, cortical amyloid load, higher Default Mode Network activity, and genetics for transfer of cognitive training gains in HOA, a logistic regression model with transfer as the dependent variable is used. All effects of the potential predictors are included as main effects. Additionally, to adjust for ACT, ACT and all interactions with ACT are included in the model as independent covariates.

To determine the impact of ACT on the structural integrity of the corpus callosum, Default Mode Network activity, BDNF, motor fitness, and VO_2_peak/VO_2_max, logistic regression models for these variables are fitted. ACT will be included as an independent variable. Additionally, the model will be adjusted for all other variables and the interactions with ACT. For example, the model for structural integrity of the corpus callosum will include ACT, Default Mode Network activity, BDNF, motor fitness, VO_2_peak/VO_2_max and all interactions with ACT as independent covariates.

Similar models will be fitted to examine the association between baseline physical activity and the structural integrity of the corpus callosum, Default Mode Network activity, and BDNF. Here, baseline physical activity and all possible interactions with baseline physical activity will be additionally included as independent covariates.

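### The models for the effect of ACT include neither center nor a pre-ACT value, although ACT is given only in Cologne and 89% of the trained non-ACT subjects are at other sites

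*Protocol article*

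**What the plan says.** Under Analysis of secondary endpoints, the protocol article sets out a model for a stated purpose: "To determine the impact of ACT on the structural integrity of the corpus callosum, Default Mode Network activity, BDNF, motor fitness" and oxygen uptake. Each variable gets a logistic regression with ACT as an independent variable, adjusted for all the other variables and their interactions with ACT. For callosal integrity the covariates are spelled out: ACT, Default Mode Network activity, BDNF, motor fitness, VO2 and the ACT interactions. Center is not listed, nor is the subject's value before ACT.

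The design facts that bear on this are:

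- **ACT is confined to one site.** "72 subjects at the German Sport University Cologne will undergo the extended experimental protocol" (Statistics, Sample size).
- **Most trained subjects without ACT are elsewhere.** The recruitment split gives "Mainz: *N* = 60, Rostock: *N* = 60" (Population, Sample size).
- **There is a small non-ACT group in Cologne.** "15 HOA will be enrolled in Cologne undergoing the standard experimental protocol without ACT". Its stated purpose is a different one: "to assure that the net effect of the cognitive training does not differ from the effects at the other trial sites".
- **Allocation is random inside sites only.** "Within each trial site, participants will be distributed randomly to experimental or control groups".
- **Some measurements precede ACT.** The Cologne protocol adds a fitness evaluation "as well as an additional MRI scan evaluation" (Study design). Under Genetics, blood is drawn "at the pre-ACT-training phase, post-ACT-training phase, and post-cognitive-training phase in Cologne".

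Change values are used in the secondary analyses, but only for fitness changes: their correlation with integrity changes, and their interaction with integrity in the transfer model. The sentence that adds center number to the models stands under the primary endpoint.

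**The concern.** ACT and site are nearly the same variable here. If every trained subject enters the model, the ACT coefficient mainly compares Cologne with Mainz and Rostock. Differences in imaging, sample handling or recruitment between sites then look like an effect of 20 weeks of training, or hide one. The only randomised ACT contrast in the trial is the one inside Cologne, and the model as written swamps it with 120 subjects who could never have been allocated to ACT.

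At stake are the trial's statements on whether physical training changes callosal integrity, network activity and BDNF. These are secondary results; the primary analysis is a separate model.

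**Working it through.** **Inputs from the document.** ACT: 72, all in Cologne. Trained without ACT: 15 in Cologne, 60 in Mainz, 60 in Rostock. Dropout: about 15%.

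**The plan's own figures.** 60 + 60 + 72 = 192, and 192 + 15 + 30 retest controls = 237, as stated. The ACT-impact models carry no power or precision figure, so there is none to reproduce for them.

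**Share of a site offset that enters the ACT coefficient.** The non-ACT group has 15 + 120 = 135 subjects, and 120/135 = 0.89. If Cologne differs from the other sites by d SD for reasons other than ACT, an unadjusted ACT coefficient is biased by 0.89 × d.

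**False-positive rate with no true ACT effect.** The documents give no offset, so d is an assumption.

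- Continuous outcome: SE = √(1/n_ACT + 1/n_nonACT), and rate = Φ(bias/SE − 1.96) + Φ(−bias/SE − 1.96).
  - 72 versus 135: SE = √(1/72 + 1/135) = 0.146 SD.
  - 61 versus 115, after 15% dropout: SE = √(1/61 + 1/115) = 0.158 SD.
- Binary outcome: the plan names logistic regression but the article gives no cut-off, so a median split is assumed, with ACT as the only covariate. The rates are the share of 40,000 simulated trials in which the Wald test of the log odds ratio is significant. At d = 0 this share is about 6%.

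| Assumed offset d | Bias | Continuous, 72 v 135 | Continuous, 61 v 115 | Median split, 72 v 135 | Median split, 61 v 115 |
|---|---|---|---|---|---|
| 0.2 SD | 0.18 SD | 23% | 20% | 17% | 16% |
| 0.3 SD | 0.27 SD | 45% | 39% | 31% | 28% |

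So the rate is roughly 15% to 45% for offsets of 0.2 to 0.3 SD. At 0.1 SD it is about 9% on the continuous scale.

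**What the fitness covariates do.** The article describes the fitness evaluation as an addition in the Cologne extended protocol. If Mainz, Rostock and the 15 Cologne controls have no motor fitness or VO2 values, a complete-case fit keeps only ACT subjects. ACT is then constant and its coefficient cannot be estimated.

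**Precision of a contrast inside Cologne.** Detectable difference at 80% power = (1.96 + 0.84) × √(1/n_ACT + 1/n_control).

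- 72 versus 15: SE = 0.284, detectable 0.80 SD.
- 61 versus 13: SE = 0.305, detectable 0.86 SD.
- Pooled comparison, 72 versus 135: 2.80 × 0.146 = 0.41 SD, but with the site bias above.

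**Uncontrolled pre-to-post change as the alternative.** SE = √(2(1 − r)/61) = 0.081, 0.057 or 0.040 SD at assumed pre-post correlations r of 0.8, 0.9 or 0.95. A time or drift effect of 0.1 SD with no ACT effect is then falsely significant in about 23%, 42% or 69% of trials. The small standard error makes a small systematic shift more damaging, so this change cannot serve as the main estimate.

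**The case against.** The strongest reply is that the comparator is inferred. The article does not say which subjects enter these models, at which visit, or whether the outcome is a level or a change. It is a condensed account that gives the covariates by way of an example, and center is addressed under the primary endpoint. This stands in part: pooling is the natural reading of a model with ACT as a yes/no term, but it is not stated. It does not remove the point. The covariate list is given, and the center sentence is not attached to these models. The other reading, with fitness measured only in Cologne, leads to a model that may not be estimable.

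Three stronger conclusions are tempting, and the documents do not support them:

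- **That a site offset will be reported as an ACT effect.** No scanner is described and no offset is given. The text shows a risk whose size is unknown. The non-ACT group also includes 15 Cologne subjects, so about 89% of an offset passes through, not all of it.
- **That the pre-ACT values go unused.** Integrity change is used in the correlation with fitness change. Nor is it shown that every outcome has a pre-ACT value: the blood draws are described for genetic work without mention of BDNF levels, and the additional MRI is not said to include resting-state imaging. The two schedule tables are not shown.
- **That the paired change in ACT subjects should replace the planned model.** It removes site but has no concurrent repeat-scan control, so it exchanges one bias for another. Adjusting the Cologne contrast for a pre-ACT value also appears infeasible, because the 15 controls follow the standard protocol, for which no scan 20 weeks earlier is described.

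**Conclusion.** The concern holds in this limited form. As written, the ACT-impact models do not separate ACT from site. Either they pool the sites, and about 89% of any Cologne difference enters the ACT coefficient, or the fitness covariates remove the comparators and ACT may not be estimable.

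The 89% follows from the planned numbers and assumes all 135 trained non-ACT subjects are in the model. The false-positive range of roughly 15% to 45% rests on an assumed offset of 0.2 to 0.3 SD. It also varies with dropout and with whether the outcome is continuous or split at the median. It comes from models with ACT as the only covariate. With the planned covariates and interactions the ACT coefficient has another meaning, and the rate could differ. This should be corrected, but it concerns secondary analyses only.

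**What to change.** Rewrite the ACT-impact models under Analysis of secondary endpoints:

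- For callosal integrity, Default Mode Network activity and BDNF, estimate the effect of ACT within Cologne. Compare the ACT subjects at the post-ACT, pre-cognitive-training visit with the 15 randomised Cologne subjects without ACT. A center term in the pooled model does the same job, because ACT is then identified only by the Cologne controls.
- State that Mainz and Rostock subjects do not identify the ACT effect.
- State which sites and groups have motor fitness and VO2 measured, and do not adjust for a variable that the 15 controls lack.
- Report the change from before to after ACT in the ACT subjects as supportive evidence only, for measures taken before ACT. Say that it has no concurrent repeat-scan control and that time and scanner drift remain in it.

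The cost is wording and precision. No new subjects or scans are needed for the callosal contrast as the design is described. For BDNF and network activity, the schedule should be checked to confirm that the 15 controls have the measure. The detectable difference is about 0.80 SD at 72 versus 15 and about 0.86 SD at 61 versus 13. The plan should say so, so that a non-significant result is not read as absence of an effect.

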**Methods:**

This 4-year interventional, multicenter, phase 2a cognitive and physical training study will enroll 237 cognitively healthy older subjects in four recruiting centers. The primary endpoint of this trial is the prediction of transfer of cognitive training gains. Secondary endpoints are the structural connectivity of the corpus callosum, Default Mode Network activity, brain-derived neurotrophic factors, motor fitness, and maximal oxygen uptake.

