#### Secondary objectives

There is evidence that physical activity and cardiorespiratory fitness are associated with reduced brain tissue loss and reduced risk for cognitive impairment in aging humans [18, 19]. Moreover, aerobic exercise training increased gray and white matter volume in the prefrontal cortex [20] of older adults and led to significant improvements of executive function [21, 22]. Further, hippocampal and medial temporal lobe volumes were larger in older adults with greater cardiorespiratory fitness [19, 23], and larger hippocampal volumes mediated improvements in spatial memory [19]. Aerobic exercise training increases cerebral blood volume [24], perfusion [25] and the adult hippocampal volume. It has been suggested that the aforementioned structural changes are mediated by neurotrophins, in particular the brain derived neurotrophic factor (BDNF) [26]. We [27–30] and others [31, 32] demonstrated that exercise induces significant increases in levels of BDNF and other growth factors, and higher serum BDNF after aerobic training was associated with larger anterior hippocampal volume [33]. Using DTI, more recent studies measured brain structural integrity as a function of cardiorespiratory fitness and aerobic exercise training in HOA. Fractional anisotropy of the corpus callosum was reported to be positively correlated to cardiorespiratory fitness in HOA [34]. Thus, cardiorespiratory fitness might modulate age-related alterations of corpus callosum integrity. In addition, greater aerobic fitness derived from a walking program was associated with increases in white matter integrity of the frontal and temporal lobes, and improvement of memory performance [14]. Consistently, using resting state fMRI analyses, it has been shown that cardiorespiratory fitness is positively associated with functional connectivity in the Default Mode Network, and that this in part mediates improved performance on tasks requiring set-shifting, task switching, and spatial working memory [35]. Furthermore, 1 year of regular walking increased functional connectivity between parts of the frontal, posterior, and temporal cortices within the Default Mode Network and the Frontal Executive Network [35]. Of note, there is evidence that the beneficial effects of physical activity on cognitive performance is not limited to cardiorespiratory fitness but is also present after resistance [36–38] and coordination exercise training [39, 40]. Moreover, different types of physical training have been shown to affect different neurocognitive networks [40, 41]. We hypothesize that coordination exercise training positively modulates cognitive transfer abilities in HOA based on the following rationale: coordination training aims at improving the efficiency of complex body movements including eye-hand coordination, bimanual coordination, leg-arm coordination, and reactions to moving objects [40]. Such complex movements require bihemispheric interactions via the corpus callosum [42], and both, size and structural integrity of the corpus callosum typically change after sensorimotor skill acquisition [43]. These interactions are probably not limited to pure motor processes but rather include selective aspects of cognition necessary for adaptive motor behavior such as attention, inhibitory and facilitatory processes, working memory, and error-related processing. In line with this, it has been demonstrated that rather anterior corpus callosum projections to the prefrontal cortex than middle corpus callosum projections to the primary motor cortex predict bimanual motor learning [44].

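### The models for the effect of ACT on the corpus callosum, DMN, BDNF and fitness adjust for ACT's own outcomes, so they do not estimate its total effect, and logistic regression does not suit most of these outcomes

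*Protocol article*

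**What the plan says.** The third paragraph of Analysis of secondary endpoints states the aim: "To determine the impact of ACT on the structural integrity of the corpus callosum, Default Mode Network activity, BDNF, motor fitness", together with VO2peak/VO2max. The method is that "logistic regression models for these variables are fitted", with ACT as an independent variable. In addition, "the model will be adjusted for all other variables and the interactions with ACT". A worked example leaves little room for another reading: "the model for structural integrity of the corpus callosum will include ACT, Default Mode Network activity, BDNF, motor fitness", VO2peak/VO2max and every interaction with ACT.

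Three other places bear on this.

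- The abstract (Methods) treats the same variables as endpoints: "Secondary endpoints are the structural connectivity of the corpus callosum, Default Mode Network activity, brain-derived neurotrophic factors, motor fitness, and maximal oxygen uptake".
- Secondary objectives reports that "exercise induces significant increases in levels of BDNF and other growth factors". It also reports a suggestion that "the aforementioned structural changes are mediated by neurotrophins, in particular the brain derived neurotrophic factor (BDNF").
- Study design and Sample size (under Population) give ACT to 72 Cologne subjects, whose schedule is "complemented by a 20-week physical training period and an evaluation of the physical fitness, as well as an additional MRI scan evaluation". Another 15 Cologne subjects follow the standard schedule without ACT. Allocation to experimental or control group is random within each site.

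**The concern.** The stated question is what ACT does to each of the five variables. In the stated model each variable is an outcome once and a covariate in the other four models. Conditioning on a variable that the intervention changes removes the part of the effect that passes through it. If ACT improves callosal integrity by raising fitness and BDNF, the integrity model could show little or no ACT effect for that very reason.

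The model type is a second problem. Logistic regression needs a two-category outcome. No such form is given for DMN activity, BDNF, motor fitness or VO2, so the models cannot be fitted as described without a cut-point that the article does not supply.

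At stake is whether the trial can say anything valid about the effect of physical training on variables that its abstract lists as secondary endpoints.

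**Working it through.** The article gives no sample size, power or effect size for these five analyses, so there is no figure of its own to reproduce.

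**1. What the adjusted coefficient estimates.** Assume a linear outcome model, no true interactions, and no unmeasured common cause of the covariates and the outcome. Let ACT shift each of k covariates by a, let each covariate have slope b on the outcome, and let c be the direct effect.

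- Total effect = c + k·a·b
- ACT coefficient after adjustment = c
- Share lost = k·a·b / (c + k·a·b), which is the mediated share m

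The integrity model has k = 4 (DMN activity, BDNF, motor fitness, VO2). The values of a, b and c below are assumptions, in SD units of the outcome.

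| a | b | c | Total effect | Adjusted ACT coefficient | m |
|---|---|---|---|---|---|
| 0.5 | 0.25 | 0 | 4 × 0.5 × 0.25 = 0.50 | 0.00 | 100% |
| 0.5 | 0.25 | 0.2 | 0.50 + 0.20 = 0.70 | 0.20 | 0.50/0.70 = 71% |
| 0.3 | 0.2 | 0 | 4 × 0.3 × 0.2 = 0.24 | 0.00 | 100% |

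Large-sample simulation agrees: a model with ACT alone recovers 0.50, 0.70 and 0.24, and the model as written, with interactions, returns 0.00, 0.20 and 0.00. After a median split, the odds ratios fall from 2.21 to 0.99, from 3.11 to 1.48, and from 1.46 to 1.00.

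Over the whole range, a total effect of 0.50 SD becomes 0.50 × (1 − m): 0.50 at m = 0, 0.25 at m = 50%, and 0 at m = 100%.

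**2. What this does to the test.** Take a total effect of 0.50 SD, fully mediated, with 72 ACT and 15 non-ACT subjects.

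- Standard error, ACT only: √(1/72 + 1/15) = √0.0806 = 0.284
- 0.50 / 0.284 = 1.76, so power ≈ Φ(1.76 − 1.96) = Φ(−0.20) ≈ 42%
- Linear model as adjusted: rejection about 5%, the alpha level
- Logistic version after a median split: rejection about 2%, with separation or non-convergence in about 32% of simulated runs (about 47% at 61 versus 13, that is, after 15% dropout)

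The failure rates follow from the parameter count. The integrity model has ACT, 4 covariates and 4 interactions: 9 slopes plus an intercept. With ACT interacting with everything, the non-ACT subjects alone must identify 5 of these 10 parameters. If only Cologne subjects are used, that is 15 people.

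**3. Model type.** For a mean shift in a normal variable, a median split has relative efficiency 2/π = 0.637, so about 36% of the information is lost. The median split is an assumption; the article states no cut-point.

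**4. Could the covariates be pre-ACT values?** The article gives no timing. It uses the same named variables as outcomes and as covariates. The pre-ACT phase belongs to the extended schedule only, and subjects without ACT have a single assessment before cognitive training. The visit that both groups share falls after ACT for the ACT group.

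**The case against.** Several points on the other side stand.

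- Callosal integrity, the outcome in the worked example, is used as high/low in the primary hypothesis and in the sample size section. For that outcome logistic regression is a defensible choice, although the caption of Fig. 2 also treats fractional anisotropy as dimensional. An analysis plan could define cut-points for the others, and dichotomising loses efficiency without invalidating a test.
- The BDNF mediation is reported only as a suggestion, and about structural changes listed before callosal anisotropy is discussed. The article does not claim that the whole effect on the corpus callosum runs through BDNF.
- The primary analysis and the ACT analyses that carry a power calculation (fitness change against integrity change, and the integrity-by-fitness interaction on transfer) do not use these models. Table 1 does not list the effect of ACT on these variables among its objectives.

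A reader might also infer more than the documents support.

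- *The ACT term cannot be estimated because fitness is measured only under ACT.* The description of the extended schedule hints at this, but the schedule tables are not shown and the Fitness examinations section does not restrict who is tested.
- *The ACT coefficient is mainly a Cologne site effect.* This depends on an analysis population that is not stated. With Cologne subjects only, it would not arise.
- *The ACT coefficient is the effect at zero VO2 and zero BDNF.* This depends on whether covariates are centred, a detail usually left to an analysis plan.
- *The baseline physical activity models have the same fault.* Those describe an association with a measured variable, and the argument about adjusting for an intervention's consequences does not carry over without separate reasoning.

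None of this answers the core point. The adjustment set is stated outright and contains ACT's own outcomes.

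**Conclusion.** The concern holds in two parts. First, with covariates measured after ACT, the only reading that fits the visits both groups share, the ACT coefficient is not the total effect that the section sets out to determine. The loss equals the mediated share, from none to all of the effect. The direction needs only that some of the effect runs through the other outcomes in the same direction; the size cannot be fixed from the documents. Second, logistic regression has no stated basis for DMN activity, BDNF, motor fitness and VO2, and the 36% loss applies only if a median split is used.

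The documents do not support saying that the ACT term is inestimable or that the effect is removed entirely. The point should be fixed, but it does not threaten the trial's main conclusions.

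**What to change.** Replace the paragraph with one linear regression per outcome: the value at the pre-cognitive-training visit on ACT and age, with centre as a factor or with Cologne subjects only, so that the randomised contrast within Cologne identifies ACT. Include no other post-ACT outcomes as covariates and no ACT interactions with them. Report pre-to-post change within ACT subjects as supportive and uncontrolled. If non-ACT subjects have no fitness data, that is the only analysis available for motor fitness and VO2. Put mediation through BDNF or fitness in a separate analysis labelled as such.

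The change is to wording only and needs no new data. Its cost is visible imprecision: with 72 versus 15, the effect detectable with 80% power (two-sided 5%) is about (1.96 + 0.84) × 0.284 = 0.80 SD, before any dropout. That limit comes from the design; the present wording hides it.
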